## Abstract

**Background:**

In total knee arthroplasty (TKA) a flexible intramedullary rod can be used to account for sagittal bowing of the distal femur. Although patients report better post-operative functional outcome when the flexible rod was used, it is unknown how the use of the flexible rod affects the placement of the femoral TKA component, and how this relates to activities of daily living. It is expected that the use of the flexible rod will result in a more flexed femoral component, a larger patellar tendon moment arm, and consequently in better functional outcome. The goal of this study is to compare the flexible rod to the standard intramedullary rod in primary TKA in terms of fit of the TKA, functional outcome, and sizing of the femoral component.

**Methods:**

A single-blind randomized controlled trial with two groups (flexible vs standard rod), with patients blinded for group allocation, and 2 years post-operative follow-up. The fit of the TKA is quantified by two parameters: (1) the flexion angle of the TKA in the sagittal plane and (2) the sagittal profile of the distal femur compared between the pre-operative bone and the TKA. Both parameters are calculated in 3D volume images obtained using fluoroscopy. Functional outcome will be measured using (1) the timed Get-up and Go test (2), the stair climbing test (3), knee power output, and (4) patient and clinician reported outcomes. Different parameters will be measured during the TKA procedure to account for the invisibility of cartilage in the 3D volumes and to study if the amount of bone removed during the procedure is affected by group allocation.

**Discussion:**

The sagittal fit of TKA is not a standardized outcome measure. We discuss our choice of parameters to define the sagittal fit (i.e., flexion angle and sagittal profile), our choice for the parameters we measure during the TKA procedure to account for the lack of cartilage thickness in fluoroscopy, and our choice for the parameters to study if the amount of bone removed during the procedure is affected by group allocation. Lastly, we discuss the merits of this planned trial.

**Trial registration:**

Netherlands Trial Register, 4888, registered 30 March 2015. https://www.trialregister.nl/trial/4888

## Background

Total knee arthroplasty (TKA) is a cost-effective surgical procedure for degenerative knee osteoarthritis. Although TKA has good long-term results, there are still some patients with poor long-term results [13]. Also, the good results are not always related to patient satisfaction and functional outcome [3, 7]. This may be caused by the fact that the kinematics of the TKA do not properly mimic the kinematics of the natural knee. Manufacturers of TKAs have addressed this by integrating aspects of natural knee kinematics into their TKA designs and instruments [9].

One aspect influencing natural knee kinematics is sagittal placement of the femoral component [18]. The instruments used for alignment of the femoral component are classically used intramedullary, and implanting the femoral component can be performed either according to the longitudinal axis of the femur in the sagittal plane or according to the anatomy of the distal femur, taking into account sagittal bowing of the femur. The amount of sagittal bowing can differ between individuals [30], and therefore to account for sagittal bowing during placement of the femoral component, a flexible intramedullary rod (flex rod) can be used instead of the standard intramedullary rod [17].

Up till now, the literature has not been conclusive which of the rods should be used, and acknowledges the dilemma of implanting the femoral component either according to the anatomy of the distal femur, or according to the longitudinal axis of the femur in the sagittal plane, thus ignoring sagittal bowing. The standard rod is considered a safe option. However, it is hypothesized that with the flex rod, less bone needs to be removed because the femoral component better fits to the natural anatomy of the distal femur in the sagittal plane. This would lead to more natural femorotibial kinematics through increasing the patellar tendon moment arm, and thus the possibility for larger knee power output without influencing muscle strength. This effect has been found in a modeling study [24] and could potentially lead to better functional outcome in vivo. Indeed, patient-reported functional outcome is higher up till 2 years in patients operated using the flex rod when compared the standard rod [17]. It is expected that due to less oversizing in the TKA procedure using the flex rod activities of daily living (ADL) such as stairclimbing, and rising from a chair can be performed more optimally [6]. Marra et al. have also shown in their modeling study that less oversizing resulted in better patellofemoral kinematics during rising from a chair [24]. It is also expected that with the use of the flex rod, the proper fit of the TKA will result in an overall smaller size chosen by the surgeon, as has been found in a retrospectively analyzed cohort and a modeling study [8, 17].

## Methods/design

### Aim

The primary aim of this study is to compare the flex rod with the standard rod in terms of post-operative sagittal fit of the distal femur. In addition, sizing and post-operative functional outcome will be evaluated.

### Design and setting

A single-blind randomized controlled trial with two groups (flex rod vs standard rod), with the participants blinded for group allocation. Participants will be measured on five occasions in our outpatient clinic (pre-operative, per-operative/post-operative, 3 months, 1 year, and 2 years post-operative). The study ends after 2- year follow-up. The trial has been set up according to CONSORT guidelines [29], and ethical approval for this study was obtained from *Medisch-ethische toetsingscommissie Slotervaartziekenhuis en Reade* (approval ID P1453).

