### Primary study parameter

The flexion angle of the TKA in the sagittal plane is measured to determine difference in femoral component placement between the groups. This angle is commonly defined as the angle ‘*γ*’ between the bone stub axis (BSA) of the femur [25] and the neutral line of the femoral component of the prosthesis [12] (Fig. 3). Due to artifacts in the fluoroscopic assessment caused by the metal in the prosthesis, the neutral line is unidentifiable. However, the most anterior plane on the inside of the femoral component of the prosthesis, the frontal flange, can be detected in the fluoroscopic assessment (Fig. 3). Therefore, the angle ‘*θ*’ between the frontal flange and the BSA is measured. The angle between the frontal flange and the neutral line is 97°; thus, the formula *γ* = *θ* − 7° can be used for future comparison between gamma and theta measurements. To obtain the angle ‘*θ*’, the BSA is aligned with the vertical *y*-axis by coronal and sagittal rotating the 3D volume image. Furthermore, the transversal plane is rotated towards an anatomic orientation to correct any femur rotation deviations from acquisition. The latter is necessary to be able to compare different cases. Once the orientation of the femur is standardized within the 3D volume image, the frontal flange can be manually annotated and compared with the *y*-axis, the BSA. For annotation, the sagittal slice with the most prominent frontal flange is chosen and to minimize measurement error from manual annotation an average over 5 iterations is used. We hypothesize that the flexion angle will be larger in the flex rod group (i.e., better fit to the distal anatomy of the femur, Fig. 2).

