One goal of the TKA procedure is restoration of the joint line. This would mean that the amount of implant material at the medial and lateral condyle in full extension of the knee is ± 1 mm from the native situation (DIST, Fig. 4b). A second goal is restoration of the flexion radius. This is operationalized as the amount of implant material at straight posterior at 90° of knee flexion (POST, Fig. 4b) which should be the same as in the native situation (± 1 mm). For mid flexion stability (at 30° of knee flexion), it is also important that the amount of implant material equals the native situation (FLEX30, Fig. 4b). Patellofemoral function can be determined at the trochlear slice. At PCO straight anterior (ANT, Fig. 4b), the amount of implant should equal the amount of native bone (± 1 mm). When the knee flexes, the patella rests on the medial and lateral condyles instead of in the trochlea. So also on the medial and lateral slices at 30° from straight anterior, the length will be calculated (ANT30, Fig 4b). The lengths of the sagittal profile lines are automatically calculated based on pixel density as representative for bone density. In case the segmentation of the femur is incorrect due to artifacts (caused by other bone density than the algorithm expects due to osteoporosis, sclerosis, lower radiation dose, etc.), the lengths are manually corrected. For all five lines, the length in the native situation is subtracted from the length in the component, resulting in a positive sign when the implant is bigger than the native femur (i.e., “overstuffing”), and a negative sign when the implant is smaller than the native femur (i.e., “understuffing”). The margins are defined as ± 1 mm (range of 2 mm). We hypothesize that the differences of the anterior and posterior sagittal contours on the three slices between the pre-operative situation and the post-operative image will be smaller in the flex rod group (i.e., better fit). In the images of the native femur, articular cartilage cannot be seen [20]. Therefore, an average cartilage thickness of 2 mm will be added to the lengths in the native femur [20].

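### Only participants are named as blinded, although the primary angle depends on manual image annotation: an avoidable risk of detection bias

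*Protocol article*

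**What the plan says.** The section Design and setting describes "A single-blind randomized controlled trial with two groups (flex rod vs standard rod), with the participants blinded for group allocation". The Methods paragraph of the abstract agrees: "with patients blinded for group allocation, and 2 years post-operative follow-up". Neither place, nor any other in the article, says that the person who reads the images is masked.

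The section Primary study parameter describes how the angle is obtained. The volume is rotated to a standard orientation, after which "the frontal flange can be manually annotated and compared with the *y*-axis, the BSA". On the choice of slice it says: "For annotation, the sagittal slice with the most prominent frontal flange is chosen". The result is the mean of five iterations. The same paragraph states the expected direction: "We hypothesize that the flexion angle will be larger in the flex rod group".

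In Secondary study parameters the profile lengths are computed automatically, but where artifacts make the segmentation wrong, "the lengths are manually corrected". The expected direction is stated there too: smaller pre- to post-operative contour differences with the flex rod.

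The Discussion discloses that the in-house measurement software has not yet been tested for reliability or validity.

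**The concern.** Blinding the participant protects outcomes that the participant can influence, and a component angle on a 3D volume is hardly one of them. The person who can influence it is the reader who places the annotation. Calling the trial single-blind and naming one blinded party is a positive statement of design, and it leaves this reader outside the blinding.

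If the reader can learn which rod was used and has the hypothesis in mind, small consistent choices in one direction would add to the difference between arms. The t test cannot separate that addition from a real effect of the rod. The same route exists, to a lesser degree, for profile lengths that need manual correction. With no reliability or validity data, nothing in the article shows that the measurement resists reader expectation.

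**Working it through.** **Inputs.** From Statistical analysis: means 6° and 11° (target difference 5°), SD 5° in each arm, α = 0.05, stated power 0.80, 27 per arm before dropout, 10% dropout, 30 per arm recruited. The article does not give the sidedness of the test; I take it as two-sided. The size of any systematic reading shift, *b*, is not in the article. It is an assumption, shown as a range.

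**The plan's own figure.** The dropout step reproduces: 54 / (1 − 0.10) = 60. The 27 per arm does not follow from the stated inputs. With standardised difference 5/5 = 1.0, two-sided α 0.05 and power 0.80, the exact t calculation gives 17 per arm; 27 per arm corresponds to power 0.95. That mismatch needs its own reconciliation and does not bear on blinding. I use 27 per arm because it is the evaluable number the plan fixes.

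**Standard error of the difference.** SE = 5 × √(2/27) = 1.36°.

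**What averaging does.** If one annotation has independent random error with SD *s*, the mean of five has error SD *s*/√5, about 0.45*s*. A consistent lean present in every iteration has the same mean after averaging, so *b* is unchanged.

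**Effect of an assumed shift when the true difference is 0.** The test statistic then follows a noncentral t distribution with 2 × 27 − 2 = 52 degrees of freedom and noncentrality *b*/SE. The false-positive rate is the probability of exceeding the two-sided 5% critical value.

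| Assumed shift between arms | Share of 5° target | *b*/SE | False-positive rate, 27 per arm | Same, 30 per arm |
|---|---|---|---|---|
| 0° | 0% | 0 | 5% | 5% |
| 0.5° | 10% | 0.37 | 6.5% | 6.7% |
| 1° | 20% | 0.73 | 11% | 12% |
| 1.5° | 30% | 1.10 | 19% | 21% |
| 2° | 40% | 1.47 | 30% | 33% |

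More patients do not help. At 30 per arm the same shift does slightly more harm, because the standard error is smaller. Masking the reader changes no sample-size figure.

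**The case against.** The strongest reply is that the article is silent rather than wrong. It is a condensed account, and image coding and reading order often sit in a full protocol or imaging manual. That stands in part. A reader of this review might infer that the image reader knows the allocation, or that the results will be biased; the article says neither. But the label single-blind, with participants as the one named party, is more than silence. If readers are in fact masked, the label is incomplete. If they are not, the primary outcome is exposed. Either way the text should change.

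Second, the reader's discretion is limited. The rotation is not described as manual, the slice has a stated rule, and profile lengths are automatic unless segmentation fails. This stands. For the angle, the step called manual is the flange annotation; for the profile, the manual step is conditional.

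Third, it is tempting to treat the 2.3° intra-observer difference in Statistical analysis as evidence of the likely bias. It is not. It describes disagreement between repeat measurements in a cited study and says nothing about a lean by allocation. The shifts above are assumptions.

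Fourth, one might extend the point to all functional outcomes. The article gives little support for that. The power rig is instrument-recorded, the timed tests involve no annotation, and participant blinding is the relevant protection for patient-reported scores. The clinician-reported Knee Society Score is the one part where the argument carries over.

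Finally, masking might seem futile if the image gives the group away. The angle alone would not do so. With means 6° and 11° and SD 5°, a guess split at 8.5° is right with probability Φ(2.5/5) = Φ(0.5), about 69%, even if the planned effect is real.

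**Conclusion.** The point holds as an avoidable risk of detection bias in the hypothesised direction. It affects the primary flexion angle through the manual flange annotation and, to a lesser extent, the sagittal profile through conditional manual corrections. Averaging five iterations does not address it.

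Its actual size cannot be derived from the article. Under the plan's SD and 27 per arm, a two-sided test and no true difference, a shift of 0.5° would do little harm (6.5%), 1° would about double the error rate (11%), and 2° would raise it to about 30%. The article supports neither a claim that bias has occurred nor a claim that any of these shifts is the likely one. The change is still worth making, because it protects the primary result at little cost.

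**What to change.** - Give the pre-operative and 3-month volumes study codes that carry no rod allocation, and present them in random order. Both sets matter, because the profile subtracts native lengths from component lengths.
- Have the existing reader or readers complete slice choice, flange annotation and every manual length correction before the codes are broken.
- Read the primary angle without surgical data. After the angle is locked, release prosthesis size only, because the profile needs a calibration set specific to size.
- Where feasible, withhold allocation from the person scoring the Knee Society Score.
- Restate the design as participant- and image-assessor-blinded. If this masking is already in place, saying so is enough.

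The cost is the recoding work and a short change of text, with no extra reader, procedure or patients. One weakness remains: the Background expects smaller components with the flex rod, so prosthesis size may give the profile reader a partial hint of allocation. Locking the angle first keeps that hint away from the primary outcome.

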### Participants

Subjects will be selected from the waiting list for patients scheduled for elective TKA in our hospital. Inclusion and exclusion criteria are shown in Table 1. Eligible subjects will be contacted, after their surgeon’s consent, by phone by a research nurse explaining the study. When they are interested in participating, the patient information sheet will be send. Eligible patients are contacted again after a minimum of 1 week for verbal consent. Written informed consent is obtained at the first study contact in our outpatient clinic.

**Table 1 Tab1:** The inclusion and exclusion criteria of the subjects

Type	Description
Inclusion criteria	• Patient with non-inflammatory knee osteoarthritis which is radiologically confirmed and which requires total knee replacement. • Age between 40 and 75 years, inclusive. • Patient plans to be available for follow-up until 2 years post-operative. • Patient is in stable health and is free of or treated for cardiac, pulmonary, hematological, or other conditions that would pose excessive operative risk. • Patient has < 10° fixed (non-correctable) varus or valgus deformity of the knee.
Exclusion criteria	• Patient has a BMI > 35. • Patient’s expected physical activity after surgery is 2 or less on the UCLA Activity Scale. • Patient has had previous hip or knee replacement surgery in the last 6 months or is planned to have a (second) hip or knee replacement in the next 6-12 months (because of the effect on function). • Patient has had a previous hip replacement on the affected side (this may cause for a restriction for the rod placement during surgery). • Patient has had major, non-arthroscopic surgery to the study knee, including HTO. • Patient has an active, local infection or systemic infection. • Patient has physical, emotional, or neurological conditions that would compromise compliance with post-operative rehabilitation and follow-up. • Bone stock compromised by disease, infection, or prior implantation which cannot provide adequate support and/or fixation to the prosthesis. • Severe instability of the knee joint secondary to the absence of collateral ligament integrity and function. • Severe instability of the knee joint due to loss of cartilage reported as “substance loss.” • Patient has knee flexion < 90°. • Patient has fixed flexion deformity >10° (passive extension lag). • Patient has >30° extension deficit (active restraint to extension). • Patient does not have a proper functioning patella tendon on the affected side measured as inability of active extension of the knee. • Patient has quadriceps weakness on the affected side; score on MRC scale < 4. • Patient has rheumatoid arthritis, any auto-immune disorder, or immunosuppressive disorder.

### Description of materials

All participants will receive the posterior stabilized model Triathlon (Stryker, Mahwah, NJ, USA). This model is used to standardize the posterior placement of the femoral component (in contrast to a cruciate-retaining model), which is expected to yield differences in the anterior part of the distal femur and therefore differences in patellofemoral function between the groups.

### TKA procedure

The surgical technique is a standardized bone-referenced technique. A tibial bone cut is made based on the standard extramedullary jig from the system aiming at resection of 9 mm bone from the unworn lateral side, or 3 mm below a worn medial compartment. The amount of valgus of the distal cut femur jig is set on the femur angle measured on hip-knee-ankle radiographs of the individual patient. A special custom-made aiming device with an offset of 5 mm (for the flex rod) and 10 mm (for the standard rod) referencing from the intercondylar notch is used to standardize the entry points of the two rods (Fig. 1). Sizing of the femur component is done with posterior referencing. Standard 3° of femoral external rotation is used in these series. Necessary soft tissue releases are done for gap balancing. A standard patella resurfacing is done, and the total implant is placed cemented.

**Fig. 1 Fig1:**
[figure not shown]
The custom-made aiming device used to standardize the distal entry points of the two rods. The device has a small cylinder which is placed in the intercondylar notch, and two holes, all interspaced at 5 mm. The anterior and posterior holes are used to mark the entry point for the standard rod and flex rod, respectively

### Investigational product

For this study, the difference between the two groups is the use of the flex rod or the standard rod during TKA. The rods are used in TKA to position the femoral component in the correct sagittal orientation (Fig. 2). The difference between the two rods is that the flex rod allows for bowing in the sagittal plane, thus following the natural anatomy of the femur. There are no extra risks involved with use of the flex rod. Both rods are part of the operating instruments used for placement of the TKA (Stryker, Mahwah, NJ, USA).

**Fig. 2 Fig2:**
[figure not shown]
The difference between the standard rod (shaded in background) and the flex rod (clear in foreground) shown in the sagittal view of the distal femur

### Study parameters

The fit of the femoral component is quantified in two parameters: the flexion angle of the TKA in the sagittal plane (Fig. 3), and the sagittal profile at three slices: medial, lateral, and at level of the trochlea (Fig. 4). Both parameters will be measured in a 3D volume image of the knee, reconstructed from images obtained with fluoroscopic assessments using the MultiDiagnost Eleva (MDE, Philips, Amsterdam, The Netherlands). All reconstructions and measurements are performed with custom-written software using Matlab (The MathWorks, Natick, MA, USA), and results are exported to a data sheet for analysis.

**Fig. 3 Fig3:**
[figure not shown]
The flexion angle (*θ*) of the prosthesis. This angle is measured in the sagittal plane between the longitudinal bone stub axis (BSA) and the frontal flange (FF). The double arrows are used for determining the orientation of the BSA. The angle *γ* between the neutral line of the femoral component (*N*) and the BSA is calculated by *γ* = *θ* − 7°

